### **Measures**

***A complete summary of the list of assessment measures and time points administered are provided in Table 2. The primary outcome measures are provided in more detailed below.***

***Psychiatric symptoms (baseline only).*** Participants will complete the Mini-International Neuropsychiatric Interview (MINI) to confirm eligibility at baseline (i.e., absence of exclusionary psychiatric condition). The MINI 7.0 is a short, structured diagnostic interview developed to assess psychiatric disorders according to DSM-5 criteria, focusing on current symptomatology.

***Medical diagnoses and medications.*** Participants will report any known medical diagnoses and current and past medications to confirm eligibility at baseline. We will follow-up monthly during treatment to see if any changes have occurred and again at follow-up.

***Demographics and military characteristics (baseline only).*** Participants will complete a demographic questionnaire to record their age, gender, years of education, socioeconomic status, branch of service, years and position in military, highest rank at discharge, and years since actively serving in the military.

***The Eating Disorder Examination (EDE) interview*** (baseline, mid-treatment, post-treatment, 6-month follow-up) is considered the gold-standard assessment for BED and has strong psychometric properties. The EDE interview uses diagnostic algorithms to diagnose BED, as well as subclinical BED, frequency of binge eating, compensatory behaviors (purging for exclusion), as well as restraint and shape and weight concerns.

***The Binge Eating Scale*** (BES) (baseline, mid-treatment, post-treatment, 6-month follow-up) provides a dimensional score of binge eating. The BES consists of 16 items; 8 items describe binge eating behaviors and 8

describe feelings and cognitions associated with binge eating. The BES yields a continuous measure of binge eating pathology (range=0–46).

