*There is a risk of injury.* In the ROC arm, Veterans will be encouraged to increase their physical activity. Although research staff will help tailor the physical activity recommendations to a Veteran's physical or medical status, it is possible that improper or vigorous physical activity could be associated with injury or discomfort. In order to address this risk, Veterans will self-report orthopedic problems, gait disturbances, and medical status prior to enrolling in the study. All participants will be instructed to alert the research team of any injury sustained as soon as possible. If an injury has occurred, we will request that the participant follow-up with his/her primary care provider before continuing with the physical activity recommendations in the study.

*Risk of loss of confidentiality as a direct result of participation in the recruitment, screening, assessment and treatment.* There is a very small risk that identified data may be compromised as part of this study. All data collected during the study assessments or treatment is de-identified and only labeled with an ID number, no name or other identifying information. With regards to paper forms, consent forms with identifying information are stored in a locked room in a locked filing cabinet. Hard copies of de-identified data is stored in a separate locked room in a locked filing cabinet. Any electronic document with identifiable information is password protected and the password is only provided to essential study staff who need to access that document to aid in the conduct of the study. Electronic de-identified data is stored on encrypted firewall protected UCSD servers or on REDCAP and only accessible by study staff. Participants will not be identified in any reports or publications. Appropriate parties other than the UCSD research staff may be granted access to the study data as required (e.g., the sponsor of this study, the Department of Defense, UCSD IRB personnel, medical monitors, or other similar entities); these individuals will be bound by the same rules of confidentiality as the investigative team not to reveal the participant's identity to others. The only time confidentiality will purposefully be broken is when required by law if the study team receives information that a participant is a threat to him/herself, another specified target, or regarding actual or reasonably suspicious child, dependent adult, or elderly abuse or neglect.

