**Stopping rules:** In this minimal risk intervention trial, it is more likely that drop-outs or difficulty in recruiting adequate numbers of participants will require stopping the trial, than that of excess adverse events will occur and require stopping the trial. However, as outlined elsewhere, we will monitor injury rates in all participants and the safety officer, together with the study investigators, will alert the IRB and the DOD if a larger than reasonably expected injury rate should occur in the treatment group.

**Measurement and reporting of adverse events.** Serious adverse events will be those that result in death, are life threatening, require (or prolong) hospitalization, cause persistent or significant disability/incapacity, result in congenital anomalies or birth defects, or are other conditions which, in the judgment of the investigators, represent significant hazards. Serious adverse events will be reported by the PI verbally and in writing as soon as possible to the IRB and

as appropriate to the DoD. Adverse events will be those that include any unfavorable and unintended diagnosis, symptom, sign, syndrome or disease which either occurs during the study, having been absent at baseline, or, if present at baseline, appears to have worsened. All adverse events (serious and non-serious, expected and unexpected) will be reported to the UCSD IRB at timelines according to appropriate guidelines (e.g., expected and not study related at IRB continuing review; unanticipated problems involving risk to participants within 10 working days) and reported to the study monitor quarterly if anticipated and not study related, or within the same timeline as reporting to the IRB if sooner than quarterly. All unanticipated problems involving risk to subjects or others will be promptly reported to the UCSD IRB and the DoD.

Blinded adverse events data will be presented to the study statistician, the PI, and the safety officer throughout this trial. The adverse event log will be used by the study staff to report injuries that may be associated with this intervention. Very few injuries are expected, as the main focus of treatment is changing eating behavior. The physical activity recommendations will include both vigorous and lifestyle physical activities, which can be adapted to the Veteran's physical or medical status.

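### The adverse event log admits injuries by suspected cause, although the protocol promises injury rates in all participants; injuries may be under-recorded, more so in CBT

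*Protocol*

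**What the plan says.** All safety statements below are in protocol section 15 unless noted.

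- Under the stopping rules, the scope is everyone: "we will monitor injury rates in all participants". The alert is raised "if a larger than reasonably expected injury rate should occur in the treatment group".
- Under measurement and reporting of adverse events, the definition carries no attribution test: "Adverse events will be those that include any unfavorable and unintended diagnosis, symptom, sign, syndrome or disease which either occurs during the study". The reporting duty is equally wide: "All adverse events (serious and non-serious, expected and unexpected) will be reported to the UCSD IRB". Events judged unrelated are not exempt; they are "reported to the study monitor quarterly if anticipated and not study related".
- The same subsection then describes the recording tool: "The adverse event log will be used by the study staff to report injuries that may be associated with this intervention".
- Under the risk of injury, the means of capture is: "All participants will be instructed to alert the research team of any injury sustained as soon as possible". That paragraph ties the anticipated injury risk to the encouragement of physical activity in ROC.
- The table of review frequencies under Data Safety and Monitoring sets a quarterly review of adverse event rates, with injuries as the named content.
- Section 9, Measures, under medical diagnoses and medications, schedules the regular check: "We will follow-up monthly during treatment to see if any changes have occurred and again at follow-up". The assessment table lists it at baseline, during treatment, post-treatment and 6 months.
- Table 1 gives ROC a physical activity component and CBT none.

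**The concern.** A rate for all participants needs a record of all injuries. A log limited to injuries that staff think the intervention may have caused is a different numerator. The two coincide only if staff consider every injury possibly related.

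The condition may also act unequally. When an injury is reported in ROC, staff have a ready mechanism in the activity advice. In CBT they have none. The protocol states masking for the dietary interviewers and for the fidelity raters of interviews, but not for whoever keeps the log. Blinding the adverse event data when they are presented later does not restore injuries that were never entered.

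At stake is the quarterly injury review, and with it the alert to the IRB and the funder. If the log feeds that review, the rates seen are too low by an unknown amount, and the shortfall may differ by arm.

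**Working it through.** The protocol states no injury rate, alert threshold or power for injuries, so there is no figure to reproduce. The check is mainly a comparison of text.

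**Step 1. Scope of each statement in section 15.**

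| Statement | Both arms? | Test of cause? |
|---|---|---|
| Monitoring of injury rates | Yes | No |
| Adverse event definition | Yes | No |
| Reporting to the IRB | Yes | No; relatedness affects timing only |
| Participants' instruction to report injuries | Yes | No |
| Entry in the adverse event log | Not stated | Yes |

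The log sentence is the only one that conditions on cause. Relatedness decides when and to whom an event is reported, which presupposes that unrelated events have been recorded somewhere. The log is the only recording tool named.

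**Step 2. Capture before the log.** The instruction to report covers both arms and any injury, but it depends on the participant acting on it. The medical check is active and is scheduled alike in both arms, but injuries are not named in it. A sprain that brings no new diagnosis or medication can pass through it unmentioned. Between week 20 and week 44 no such check is scheduled: (44 − 20) / 44 = 24 / 44 = 55% of the study period. The instruction to report has no stated end date, so this is a gap in active questioning, not in all capture.

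**Step 3. What the entry condition can do (illustration only).** Assumptions: 60 per arm (120 in total; no allocation ratio is stated), a true injury risk of 10% in both arms, and pass shares chosen to show a range. Logged injuries per arm = 60 × 0.10 × share passing = 6 × share. True total = 12 of 120.

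| Share passing, ROC / CBT | Logged, ROC / CBT | Ratio | Logged in total | Recorded share of 12 |
|---|---|---|---|---|
| 100% / 100% | 6.0 / 6.0 | 1.0 | 12.0 | 100% |
| 80% / 80% | 4.8 / 4.8 | 1.0 | 9.6 | 80% |
| 80% / 40% | 4.8 / 2.4 | 2.0 | 7.2 | 60% |
| 80% / 20% | 4.8 / 1.2 | 4.0 | 6.0 | 50% |

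The ratio and the recorded share do not depend on the 10%. At risks of 5% and 20% the counts halve or double and both columns stay the same. The table shows two things. Any share below 100% lowers the overall rate, even when it is equal in both arms. The ratio between arms moves only when the shares differ.

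**The case against.** The strongest reply is that the log is not the sole channel. All adverse events must go to the IRB, and unrelated ones to the study monitor each quarter. The log sentence does not say that other injuries are excluded, and the intervention it refers to is not defined as ROC. Nor does the protocol say that the quarterly rates come only from the log. All of this stands. It limits the point to what may happen. It does not remove the conflict, because a duty to report is not a method of recording, and no other method is named.

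A reader might infer several stronger claims that the documents do not support:

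- **That CBT injuries are largely screened out.** No share of injuries judged related is given for either arm, so this cannot be shown.
- **That injuries are known only if volunteered.** Every participant is told to report any injury, and the medical check can bring some to light.
- **That ROC participants get more prompts to mention injuries.** Contact frequency and time are matched, and both arms set goals.
- **That the alert has lost its valid comparator.** The alert is set against a reasonably expected rate, not against CBT, and no comparison of injuries between arms is planned. Complete logging would not make such a comparison decisive. With 6 v 12 injuries among 60 per arm, the pooled risk is 18/120 = 0.15, the standard error is √(0.15 × 0.85 × 2/60) = 0.065, and z = 0.10 / 0.065 ≈ 1.5.
- **That a large spurious ratio between arms is to be expected.** Any such figure comes from assumed fractions. With equal shares the ratio is 1.0.

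The low-risk status of the trial and the few injuries expected also count against treating this as grave.

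**Conclusion.** The point holds as an internal conflict with a plausible direction and an unknown size. Section 15 promises injury rates in all participants and defines adverse events without regard to cause, but gives its log an entry condition based on cause. The condition may lower the recorded injury rate, and may do so more in CBT because activity is prescribed only in ROC. That direction assumes that unmasked staff find an injury easier to link to ROC than to CBT, and that the quarterly rates draw on the log. Both are reasonable readings; neither is stated. The missing injury question adds to the risk of under-recording in both arms. This is a cheap improvement worth making, not a threat to the efficacy analyses.

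**What to change.** 1. Reconcile section 15 by removing the causal condition from the log's entry rule, so that every reported injury in either arm is logged.
2. Record relatedness as a separate field after entry.
3. State that the injury rates reviewed quarterly are computed from all logged injuries, whatever their relatedness.
4. Add one injury question, worded identically in both arms, to the existing monthly check during treatment and to the post-treatment and 6-month checks.

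A single web survey midway through follow-up would shorten the 24-week interval without active questioning. It is optional.

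The cost is one survey item at contacts already scheduled and a longer log that will include unrelated events.

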## **16. PRIVACY AND CONFIDENTIALITY CONSIDERATIONS INCLUDING DATA ACCESS AND MANAGEMENT**

We will implement the following security plan to promote security of the data and privacy of the participants. Data collection will be completed with an emphasis upon maintenance of confidentiality. We plan to extract data from questionnaires and in-study behavioral measures. Only [name] and her research staff, each of whom has mental health clinical training and UCSD clearance will have access to any personal health information collected. We will assign participants a study identification number unrelated to identifying information. The study ID number will be used by participants on their questionnaires and data collection forms. The only materials containing subject identifying information will be the consent and HIPAA forms. We will create a master list linking the de-identified study identification number to the participant's record. The record in the master list will be identified by a randomized participant number provided by our statistician. The master list will be maintained by [name] in her laboratory. There will be only one password protected electronic version of this file. Access to the master list will be limited to the P.I.s and their designees, all of whom will have completed DoD and UCSD IRB training requirements. At the earliest opportunity and no later than 36 months following data analysis, the master list (i.e., the only source that links the study identification numbers to the individuals) will be destroyed.

The online screen will be set up through Research Electronic Data Capture (REDCap). REDCap is a secure web-based application built around HIPAA guidelines to support data capture for research studies. UCSD's Clinical and Translational Research Institute (CTRI) provides support to facilitating conducting research through REDCap as well as comprehensive maintenance and support. The REDCap Software sits on a dedicated server behind a firewall to eliminate all non-essential credentials. The data itself is isolated on a separate server that sits behind an additional firewall layer for added security. Interaction between REDCap and the participant is encrypted via SSL. support for the REDCap infrastructure at UCSD. Only essential staff (Data Manager, Project Coordinator, RAs) can access the data collected through REDCap through log-in credentials granted through UCSD's Business Systems Single Sign-On. De-identified data collected during treatment or in person assessments will also be entered through REDCap using the participant's ID number so only approved study staff can access the database.

Screening information received from the VASDHS will be securely stored and password protected on our UCSD servers with only study staff having access to this data.

## **17. POTENTIAL BENEFITS**

The most important potential benefit is the reduction of binge eating, which may translate into a number of favorable correlated outcomes, including improved weight loss, weight loss maintenance, and reductions in psychological distress.

## **18. RISK/BENEFIT RATIO**

There is a relatively low risk to participants and the potential to benefit from a reduction in binge eating and weight.

#### **19. EXPENSE TO PARTICIPANT**

There is no expense to participants for participating in this study. There is no cost to participate.

#### **20. COMPENSATION FOR PARTICIPATION**

All participants will receive incentives at the following levels for time and effort: baseline = \$50, mid -treatment = \$50, post-treatment = \$100, 6-month follow-up = \$150. Participants who withdraw, but who wish to have their weight and binge eating measured or self-report their weight and binge eating to study staff at follow-up time points will receive a \$25 gift card at each assessment time point (mid-treatment, post-treatment, mid-follow-up, and follow-up) that remains after the point at which he or she withdrew. Participants who enroll and complete all assessment visits can earn up to \$350.

### **23. FUNDING SUPPORT FOR THIS STUDY**

Funding for this study will be provided by the Department of Defense award number PR170320

### **24. BIOLOGICAL MATERIALS TRANSFER AGREEMENT**

Not applicable. No biological materials will be collected or transferred.

### **25. INVESTIGATIONAL DRUG FACT SHEET AND IND/IDE HOLDER**

Not applicable. No drugs will be given or investigated in this study.

### **26. IMPACT ON STAFF**

Not applicable. This study does not involve the nursing staff from UCSD and/or VASDHS.

### **27. CONFLICT OF INTEREST**

There are no conflicts of interest.

### **28. SUPPLEMENTAL INSTRUCTIONS FOR CANCER-RELATED STUDIES**

Not applicable.

### **29. OTHER APPROVALS/REGULATED MATERIALS**

None.

### **30. PROCEDURES FOR SURROGATE CONSENT AND/OR DECISIONAL CAPACITY ASSESSMENT**

Not applicable. Surrogate consent will not be used for this study.

1 Modifications to the Protocol (excluding staff and advertising changes)

2  
3 Initial approval July 2018

4  
5 January 2019

- 6 • Screening: Added a question about whether the participant received healthcare at  
7 VA San Diego Healthcare System (VASDHS) to online screen. Added permission to  
8 share information between VASDHS and UC, San Diego.
- 9 • Assessment visits: Increased baseline, post-treatment, and 6-month follow-up  
10 assessments from one visit to two visits to collect additional measures
- 11 • Assessment measures: Added the following to the demographic questionnaire: first  
12 language and primary language. Added the following measures to baseline, post-  
13 treatment and 6-month follow-up: Yale Food Addiction Scale, PTSD Checklist for  
14 DSM 5, Wide Range Achievement Test, Delayed Discounting, Matrix Reasoning  
15 Test, and Digit Symbol Coding
- 16 • Assessment measures: Changed from one mid-treatment assessment to monthly  
17 assessments for the following measures: Godin Leisure-Time Exercise, Eating  
18 Disorder Examination Questionnaire, Binge Eating Scale, Adult Eating Behavior  
19 Questionnaire, Reward Based Eating Drive Scale-13.
- 20 • Treatment: Increased the length of treatment sessions from 60 minutes to 90  
21 minutes
- 22 • Inclusion/exclusion criteria: Changed the enrollment criteria from BMI>25 to BMI  $\geq$   
23 25. Specified exclusion of individuals with Bipolar and Borderline Personality  
24 Disorder.
- 25 • Incentives: Increased and reallocated incentives in accordance with the increased  
26 number of assessments: Total of \$415 consisting of \$25 x 2 baseline assessment  
27 visits, \$5 to cover transportation x 18 treatments=\$90, \$25 for one mid-treatment  
28 assessment visit, \$100 for two post-treatment assessment visits, and \$150 for two 6-  
29 month follow-up assessment visits. Added scrips (check) as an alternative incentive  
30 to gift cards.

31  
32 March 2019

- 33 • Assessment visits: Changed randomization visit from in-person to over the phone
- 34 • Assessment measures: Added additional category for gender and race (other  
35 [please explain]), replaced primary language with preferred language, added  
36 additional category for the branch of the military, replaced rank in the military with  
37 exposure to combat, and modified income questions in the demographic  
38 questionnaire.
- 39 • Assessment measures: Added the following measures to baseline, post-treatment  
40 and 6-month follow-up: digit span, eye tracking, and Global Physical Activity  
41 Questionnaire (GPAQ). Added questions regarding weight management practices  
42 prior to participating in the study.
- 43 • Inclusion/exclusion criteria: Removed the exclusionary criteria “taking medication  
44 that may interfere physical activity”.

May 2019

- Assessment measures: Added a question requesting permission to communicate with physician for safety concerns or collecting weight information.

October 2019

- Screening: Changed from online screen to phone screen question whether they receive health care at VASDHS.

March 2020

- Requested permission from IRB to share study participants' data with VA Boston Healthcare System for another DOD funded study.

April 2020

- Screening: Added a question to determine if other family members are participating in the current study to phone screen.
- Assessment measures: Added the following questions to the demographic questionnaire: sex assigned at birth, gender identify, years served as active-duty personnel vs. reservist, branch served, positions served as active-duty personnel and when a reservist, highest rank at discharge, number of years since served in the military, whether on reserve while participating in the study.
- Recruitment: Added permission for current/former participants to share information about the study with friends and family.
- Consent: Added teleconsent, virtual assessments, and virtual treatments via password protected HIPAA compliant Zoom meetings in response to COVID-19 pandemic restrictions.
- Incentives: Added direct deposit as an incentive option to gift cards and scrips.

April 2021

- Recruitment: Added the use of BuildClinical for recruitment.

May 2021

- Increased the number of potential participants who could consent from 300 to 350 (to randomize 120 participants) since conversion rate was lower than expected.
- Incentives: Removed incentive for travel as it was no longer needed once sessions were remote.

June 2021

- Screening: Added 3 questions regarding loss of control eating to online screen.

August 2021

- Consent: Created an additional consent form which stated that treatment and assessments could be either remote or in person.

January 2022

- Screen: Added additional questions regarding loss of control eating using other language to online screen to improve detection of loss of control eating.
